### Primary outcome measure

*LDL-C level*. The primary endpoint will be the mean change in LDL-C level [time Frame: from randomization (day 0) to V5 (week 24) for a total of 6 months of treatment]. Per guideline, the LDL-C level has been validated as a primary measurement for the clinical efficacy of the treatments [3].

### Secondary outcome measures

The percentage of the participants with an LDL < 70 mg/dLThe percentage of the participants with an LDL < 70 mg/dL and an HDL > 500 mg/dLThe ratio of measured LDL to baseline LDLCoefficient of variation of LDLC-reactive protein levelMean change in body mass index (BMI)Mean score of General Self-Efficacy Scale (GSEs). The GSEs is a psychometric scale that assesses optimism in one’s ability to cope with a variety of life’s challenges. It consists of 10 items representing attitudes towards obstacles rated on a scale from 0 (not optimal) to 4 (very optimal). A Chinese version has been validated [19].Mean score of Quality of life index (QL-index). The QL-index is a tool to evaluate quality of life [20]. It was initially established to measure lifestyle factors in cancer patients and is now commonly used in various disease states. Measurements cover: activities of daily living, principal activities, health, outlook, and support [21]. We consider QL-index as valid measurements to evaluate the quality of life in ASCVD patients.

### Participant timeline {13}

The participant timeline is shown in Fig. 2.

**Fig. 2 Fig2:**
[figure not shown]
Participant timeline

### Sample size {14}

Considering the primary outcome variable as the reduction in the mean LDL-C from baseline to week 24, an absolute reduction of 20% in LDL-C is expected [22, 23]. One hundred twenty-two subjects per group was calculated initially to offer 80% power at a one-sided 0.05 significance level according to a 1:1 ratio of random grouping. Allowing for a maximum follow-up loss rate of 20% in both groups, 300 patients were determined as the target sample size—150 patients in each group.

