### Objectives {7}

Aim 1: To determine the efficacy of mobile-based CBT interventions, compared with conventional interventions, in ASCVD patients receiving standard treatments;Hypothesis 1a (primary study hypothesis): a significant reduction in objective parameters, including LDL-C level, will be demonstrated in participants randomly assigned to the CBT group relative to participants in the conventional interventions group.

Aim 2: To improve our capacity to match patients to treatments more efficiently by identifying self-efficacy, and quality of life.Hypothesis 2a: a significant improvement in self-efficacy, and quality of life, measured by scales and questionnaires, will be demonstrated in participants randomly assigned to the CBT group relative to participants in the conventional interventions group.

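### The sample size states its effect as a 20% fall in LDL-C from baseline, not as a CBT-versus-control difference, so the 80% power cannot be shown to apply to the between-arm comparison; the attrition figure is also slightly short

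*Protocol article*

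**What the plan says.** The protocol article's Sample size {14} section opens with "Considering the primary outcome variable as the reduction in the mean LDL-C from baseline to week 24" and continues that "an absolute reduction of 20% in LDL-C is expected", citing two references. It then says "One hundred twenty-two subjects per group was calculated initially to offer 80% power at a one-sided 0.05 significance level" with 1:1 allocation. On attrition it says "Allowing for a maximum follow-up loss rate of 20% in both groups, 300 patients were determined as the target sample size", which is 150 per group.

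Objectives {7} frames the primary hypothesis as a reduction in the CBT group "relative to participants in the conventional interventions group". Trial design {8} calls the study a parallel-group superiority trial. Under Explanation for the choice of comparators {6b}, controls receive patient education at each follow-up, and both arms receive standard drug treatment.

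Statistical methods {20a} names a paired-samples t-test for the primary and secondary endpoints and p < 0.05 as the threshold, without saying one- or two-sided.

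**The concern.** A fall from baseline is a within-arm quantity, whereas the hypothesis is a difference between arms. The two coincide only if the control arm does not change. The protocol does not state that assumption, and because controls are actively managed it cannot be taken for granted. Calling a percentage reduction absolute adds a second ambiguity: the 20% could be relative to baseline or a mistranslated difference in concentration units.

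The section fixes n, power, alpha and side, but it attaches them to an effect that is not the contrast in the hypothesis. A reader cannot tell what between-arm difference the trial was sized to detect. The risk is that a null result is taken as evidence against a 20% between-arm effect when the design may have had a different target.

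The attrition step also fails to close on its own figures, though by little.

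**Working it through.** **Inputs from Sample size {14}:** 20% effect; 122 evaluable per arm; one-sided alpha 0.05; power 80%; 1:1 allocation; 20% loss; 150 per arm recruited. **Not given:** SD of the LDL-C change, control-arm change, between-arm difference.

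**1. Can 122 be reproduced?** Not from the stated inputs, because there is no SD. It can only be solved backwards. For a two-sample comparison of means (normal approximation), n per arm = 2(z_α + z_β)² / d², so d = (z_α + z_β)·√(2/n).
- One-sided: d = (1.645 + 0.842)·√(2/122) = 0.318 (0.319 with the noncentral t).
- Two-sided: d = (1.960 + 0.842)·√(2/122) = 0.359.

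**2. SD implied if 20% is the between-arm difference** (SD = 20/d, as % of baseline):

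| Test assumed | Implied SD |
|---|---|
| Two-sample, one-sided 0.05 | 62.8% (62.6% with noncentral t) |
| Two-sample, two-sided 0.05 | 55.8% |

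If 20% is instead a within-arm change tested by a one-sided paired test with 122 patients, d = 2.487/√122 = 0.225 and the implied SD is 88.8%. The implied SD therefore depends on which reading is taken, and the text does not settle that.

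**3. Power if 20% is the fall in the CBT arm.** Take SD 62.8%, 122 per arm, one-sided 0.05. Control-arm falls of 5% and 10% are assumptions, not protocol figures. Power = Φ(Δ/(SD·√(2/n)) − 1.645), with SD·√(2/n) = 62.8 × 0.128 = 8.04.

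| Control fall (assumed) | Between-arm Δ | Δ/8.04 | Power, one-sided | Power, two-sided |
|---|---|---|---|---|
| 0% | 20 | 2.49 | 80% | 70% |
| 5% | 15 | 1.86 | 59% | 46% |
| 10% | 10 | 1.24 | 34% | 24% |

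**4. Sensitivity to the SD.** With an assumed SD of 30% to 40%, also not in the document, a 20-point difference needs only 28 to 50 per arm one-sided. At 122 per arm, a 20-point difference then has over 98% power and a 10-point difference has 83% to 62%. The same missing inputs can therefore make the trial look under- or over-sized.

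**5. Attrition.** 122/0.8 = 152.5, so 153 per arm (306 in total). With 150 per arm, 20% loss leaves 150 × 0.8 = 120. At d = 0.318, power with 120 is Φ(0.318·√60 − 1.645) = Φ(0.821) = 79.4%. To keep 122, the tolerable loss is 1 − 122/150 = 18.7%.

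**6. What 120 per arm detects with 80% power.** One-sided: 2.487·√(2/120) = 0.321. Two-sided: 2.802·√(2/120) = 0.362.

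**The case against.** The strongest reply is that this is loose wording, not a calculation aimed at the wrong contrast. The section speaks of subjects per group and 1:1 grouping, the design is parallel-group superiority, and the hypothesis is relative to control. If 20% was meant as the between-arm difference and the SD was near 63%, the 80% does describe a one-sided between-arm test. That reading is open, and it rules out saying that the stated power is wrong. It does not remove the problem, because the sentence as written defines the variable as a change from baseline.

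A missing SD is ordinary condensation in an article; the full protocol or the two cited references may supply it. That stands, and the missing SD alone would not be a finding. The finding is that the effect the article does state is not the contrast it tests.

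A reader might infer that 122 follows from 20% only with an SD of 63%. That holds only under a one-sided two-sample test of means; other readings give about 56% or 89%. A reader might also infer from the 59% or 34% that the trial is underpowered. The document does not support this: both figures rest on an assumed control-arm fall, and at an SD of 30% even a 10-point difference has 83% power. Eligibility criteria {10} also require current statin use, so baseline LDL-C is already on treatment in both arms, which weakens any presumption of a large control-arm fall.

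On attrition, multiplying by 1.2 gives 146.4 and could explain a rounded 150. The shortfall is indeed small, but the stated 20% loss still does not leave 122.

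**Conclusion.** The point holds in a limited form. The sample-size section expresses its effect as a percentage fall from baseline while the hypothesis is a between-arm difference, so the claimed 80% power cannot be shown to apply to that difference. The paired test in Statistical methods {20a}, with no side stated, does not resolve which comparison was meant.

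The size of the effect on power is undetermined. On the most favourable reading the 80% stands, given an unstated SD of about 63% of baseline. If 20% is the CBT-arm fall at that same SD, each point of control-arm fall reduces power, to 59% at an assumed 5%. Underpowering is not demonstrated.

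The attrition error is definite but minor: 150 per arm falls 3 short of the 153 required, giving 79.4% instead of 80% at the stated loss rate.

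**What to change.** Rewrite Sample size {14} to give:
- the target between-arm difference in week-24 LDL-C change, with its unit (mg/dL or % of baseline) and the word absolute removed or explained;
- the SD of that change and its source;
- the assumed control-arm change;
- the between-arm test and whether it is one- or two-sided, worded identically in Statistical methods {20a}.

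For the existing 300, report that 120 per arm after 20% loss detects a standardised difference of about 0.32 with 80% power at one-sided 0.05, or about 0.36 two-sided. Correct the attrition statement: either 150 per arm tolerates 18.7% loss for 122 evaluable, or 20% loss leaves 120 and 79.4% power on the original assumptions.

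This adds no patients. The cost is a rewritten paragraph and a slightly less favourable stated power.

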### Statistical methods

#### Statistical methods for primary and secondary outcomes {20a}

Categorical variables will be expressed in numerical values with their respective percentages and compared using the chi-squared test at baseline. Continuous variables will be expressed as mean ± SD and compared using the *t*-test. The significance of primary and secondary endpoints will be evaluated with the paired-samples *t*-test. A *p*-value < 0.05 indicates statistical significance. All data will be analyzed with the SPSS.

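### The 80% power rests on an unjustified one-sided 0.05 level that the analysis section does not repeat; at two-sided 0.05 the same design has about 70% power

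*Protocol article*

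**What the plan says.** Two sections of the protocol article bear on the level of the primary test.

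- **Sample size {14}** gives the group size, power and level together: "One hundred twenty-two subjects per group was calculated initially to offer 80% power at a one-sided 0.05 significance level". Allocation is 1:1. The size is then raised to 150 per group, 300 in all: "Allowing for a maximum follow-up loss rate of 20% in both groups". The expected effect is a 20% reduction in LDL-C; no standard deviation is given.
- **Statistical methods for primary and secondary outcomes {20a}** gives the criterion for the p-value as "value < 0.05 indicates statistical significance". It states no side and does not refer back to the one-sided level.

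Three other sections give context. Objectives {7} words the primary hypothesis in one direction: lower LDL-C with CBT than with the conventional intervention. Trial design {8} calls the trial an open-label, parallel-group superiority trial. Neither sets the side of the test, and no section gives a reason for a one-sided 0.05 level. Trial status reports that recruitment was completed in January 2022, although Recruitment {15} still expects it to run until 2023.

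**The concern.** The power statement is tied to a one-sided 0.05 level, but the rule for declaring success is an unqualified p < 0.05. Readers normally take an unqualified 0.05 as two-sided, and on that reading the trial does not have the power it claims. If one-sided 0.05 is meant, superiority can be declared on evidence that a conventional two-sided test would call non-significant. The discussion section of the article itself accepts that expectancy effects may bias this unblinded trial.

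The practical stake is a result favouring CBT with a two-sided p between 0.05 and 0.10. It would count as positive at the level in the sample size section and as negative under the usual reading of the analysis section. If the design effect is true, about one trial in ten of this size falls in that band (shown in the working).

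**Working it through.** **Inputs.** From Sample size {14}: 122 per group, 80% power, one-sided 0.05, 1:1 allocation, 20% loss, 150 per group enrolled. Normal quantiles: z(0.95) = 1.645, z(0.975) = 1.960, z(0.80) = 0.842.

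**Step 1: the plan's own figure.** Without a standard deviation, 122 cannot be reproduced from the 20% effect. It can be inverted. Assuming a two-sample comparison of means, the standardised difference it implies is

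d = (1.645 + 0.842) × √(2/122) = 2.487 × 0.1280 = 0.318.

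Putting d = 0.318 back at one-sided 0.05 returns 122 per group, by construction. A noncentral t calculation gives d = 0.319. As a check on the assumption, a 20-point difference between two proportions was tried, with the higher proportion from 0.25 to 0.75, one- and two-sided, with and without continuity correction. It does not give 122 at 80% power.

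**Step 2: power at two-sided 0.05, 122 per group.** The standard deviation cancels, because the expected test statistic is 1.645 + 0.842 whatever its value:

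Power = Φ(1.645 + 0.842 − 1.960) = Φ(0.527) = 70.1% (noncentral t: 70.0%).

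**Step 3: other group sizes.** Power = Φ(d√(n/2) − z), with z = 1.645 or 1.960.

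| n per group | Basis | d√(n/2) | One-sided 0.05 | Two-sided 0.05 |
|---|---|---|---|---|
| 120 | 150 × 0.80 | 2.466 | 79.4% | 69.4% |
| 122 | as calculated | 2.487 | 80.0% | 70.1% |
| 150 | no loss | 2.757 | 86.7% | 78.7% |

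Two-sided power stays below 80% even with complete follow-up.

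**Step 4: size needed for 80% at two-sided 0.05.**

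n = 2 × (1.960 + 0.842)² / 0.318² ≈ 155 evaluable per group, or 155/0.80 ≈ 194 enrolled per group, against 150 planned. This shows the scale only; it is not a proposal.

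**Step 5: the band where the conclusion depends on the side.** With 120 per group and the design effect true, the chance of a result between the two critical values is 79.4% − 69.4% = 10.0 percentage points.

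**Step 6: error if the test is one-sided 0.05.** The chance of falsely declaring CBT superior is 0.05. A two-sided 0.05 test allows 0.025 in that direction, so the ratio is 0.05/0.025 = 2. The one-sided test corresponds to two-sided 0.10.

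**Step 7: could baseline adjustment restore the power?** That depends on what the implied standard deviation describes. With 120 per group at two-sided 0.05 and an assumed baseline correlation r:

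| r | d scaled by change-score SD; variance × (1 + r)/2 | d scaled by SD of the level; variance × (1 − r²) |
|---|---|---|
| 0.3 | 86% | 73% |
| 0.5 | 81% | 81% |
| 0.7 | 76% | 93% |

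The two readings move in opposite directions as r rises, and the article gives neither the standard deviation nor r. No single adjusted power figure can be supported.

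**The case against.** The strongest reply is that the plan is coherent as a one-sided plan. The only side written anywhere is one-sided, the primary hypothesis is directional, the design is superiority, and p < 0.05 is compatible with a one-sided test. On that reading the 80% stands. The analysis plan, which is not shown, may also restate the side.

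Much of this stands. A reader might infer that the two sections contradict each other, or that the power calculation contains an arithmetic error. The article supports neither: no section specifies a two-sided test, and the 70% is conditional on one. Nor is the side left entirely open, since the sample size section does name one. The mention of chi-squared tests does not help to settle it, because the article ties them to comparisons at baseline and the primary endpoint is continuous. It is also fair that a one-sided 0.05 test holds its own 5%; the doubling is measured against the 0.025 per direction of a two-sided 0.05 test.

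The reply does not supply a reason for the lenient level, and it does not carry that level into the success criterion. These are two statements the article itself makes, so the point does not depend on what the analysis plan may add.

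A further objection is that the analysis section names a paired-samples t-test for the endpoints, so the power figures here do not describe the test as written. That is true. It is a separate defect, and the figures apply to the between-group comparison that the objectives and the per-group sample size call for.

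**Conclusion.** The concern holds in conditional form: an unjustified one-sided 0.05 level supports the stated power, and the analysis criterion does not repeat it. At two-sided 0.05, power at the design effect is about 70% with 122 per group, 69% with 120 and 79% with 150, rather than 80%. At one-sided 0.05 the 80% stands, but the standard of evidence is that of two-sided 0.10.

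The power figures assume that 122 came from a two-sample comparison of means and that the primary test is between groups. They do not depend on the missing standard deviation. The choice of side decides the conclusion for any result favouring CBT with a two-sided p between 0.05 and 0.10, so it should be settled before the data are analysed.

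**What to change.** 1. In Statistical methods {20a}, state that the primary between-group comparison is tested at two-sided 0.05 and reported with a 95% confidence interval.
2. In Sample size {14}, replace the one-sided level with the same two-sided 0.05. Restate the power of the existing 300 patients as about 70% at the design effect (69% with 120 evaluable per group, 79% if all 150 are retained), noting that the original figure was 80% at one-sided 0.05.
3. Do not add enrolment. The Trial status section reports recruitment complete.
4. Baseline adjustment may recover some power. Print no adjusted power figure unless the standard deviation, whether it belongs to the change score or the level, and the baseline correlation are all stated.

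The cost is wording in two sections and a less favourable power figure. The paired-samples t-test needs its own correction.

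### 150 per group keeps the required 122 evaluable patients only up to 18.7% loss, slightly short of the 20% the protocol allows for

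*Protocol article*

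**What the plan says.** All the figures stand in the Sample size section {14} of the protocol article.

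- **Requirement:** "One hundred twenty-two subjects per group was calculated initially", and this number is said "to offer 80% power at a one-sided 0.05 significance level", with 1:1 allocation.
- **Loss allowance:** "Allowing for a maximum follow-up loss rate of 20% in both groups".
- **Target:** "300 patients were determined as the target sample size—150 patients in each group".
- **Effect:** "an absolute reduction of 20% in LDL-C is expected". No standard deviation is given, and no formula is named for the step from 122 to 150.

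Two other sections bear on what a lost patient costs. The primary outcome is the change in LDL-C from randomization to week 24. The section on non-adherence and missing data {20c} rules out imputation and limits every analysis to observed cases.

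**The concern.** The sentence presents 150 per group as enough to absorb losses of up to 20%. A reader expects at least 122 patients per group to remain at that loss rate, because 122 is the number the section ties to 80% power. Fewer than 122 remain.

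The loss allowance matters here because a patient with no week-24 LDL-C value adds nothing to an observed-case comparison of the change to week 24. Enrolling extra patients is the only protection of the evaluable number that the article describes. At stake is whether the stated power holds at the loss rate the plan itself names.

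**Working it through.** **Inputs, all from the Sample size section {14}:** 122 per group required; 80% power; one-sided alpha 0.05; 1:1 allocation; maximum loss 20% in both groups; target 150 per group, 300 in total.

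**1. The plan's own figures.** The 122 cannot be re-derived, because no standard deviation is stated. It is taken as given. For the target, the usual allowance divides by the fraction retained:

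- 122 / (1 − 0.20) = 152.5, rounded up to 153 per group, or 306 in total.
- The stated target is 150 per group, 300 in total. The exact figure is 153/150 = 1.02 times the stated one, a difference of 2%.

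The target is therefore close to the exact figure but below it.

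**2. What remains at the stated maximum loss.** 150 × (1 − 0.20) = 120 per group, which is 122 − 120 = 2 short.

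**3. The loss that 150 per group can absorb.** 1 − 122/150 = 28/150 = 18.7%. Up to 28 patients per group can be lost with 122 kept. At the full 20%, 30 are lost.

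**4. Power at 120 per group.** With no standard deviation stated, the standardised effect d has to be worked back from 122. Using the normal approximation for two means:

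- d = (1.645 + 0.842) × √(2/122) = 0.318, if 122 gives exactly 80%.
- Power at n per group = Φ(d × √(n/2) − 1.645).
- At n = 120: 0.3184 × √60 = 2.466, and Φ(2.466 − 1.645) = Φ(0.821) = 79.4%.
- A noncentral t calculation gives d = 0.319 and the same 79.4%.

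**5. Sensitivity to rounding of the 122.** If the formula gave a value just above 121, rounded up to 122, then d is about 0.3197. Power at 120 is then Φ(0.3197 × √60 − 1.645) = Φ(0.831) = 79.7%.

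| Patients per group in the analysis | Loss from 150 | Power if 122 gives exactly 80% | Power if 122 was rounded up from just above 121 |
|---|---|---|---|
| 122 | 18.7% | 80.0% | slightly above 80% |
| 120 | 20.0% | 79.4% | 79.7% |

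The shortfall of 2 patients per group needs no assumption about the standard deviation. Only the power figures do.

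**The case against.** The strongest reply is that this is rounding and nothing more. The exact total of 306 and the stated 300 differ by 2%, and 300 is a convenient number. The article calls 20% a maximum, not an expected rate, and at any loss up to 18.7% the requirement is met. Even in the worst case the cost is 0.3 to 0.6 points of power, which is small beside the uncertainty in a requirement whose standard deviation is not given. The Trial status section also reports recruitment completed in January 2022, so the target may no longer be open to change.

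Most of this stands, and it fixes the size of the point: minor, and a matter of wording. Two parts do not remove it. Rounding to a convenient total is harmless when it goes up; here it went down, so the allowance is not fully met. And because 20% is given as the maximum allowed for, the design claims to hold at that rate. Between 18.7% and 20%, inside the plan's own allowance, it does not quite hold.

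A reader might infer that the wrong formula was used, multiplying by 1.2 instead of dividing by 0.80. The documents do not support this. 122 × 1.2 = 146.4, which rounds up to 147, not 150. The stated figure lies 3 above 147 and 3 below 153, so it points to neither formula, and the article names none. Rounding 306 down to 300 accounts for the text at least as well.

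**Conclusion.** The point holds as a small inconsistency within one section. The target of 150 per group keeps the required 122 evaluable patients up to 18.7% loss, not up to the stated 20%. At 20% loss, 120 per group remain, and power is about 79.4% to 79.7% instead of 80%. Rounding down from 306 to 300 is the probable source, although the article does not show the step.

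The counts follow directly from the stated figures, given that patients lost before week 24 drop out of the primary comparison. The power range rests on two further assumptions: a two-group comparison of means at one-sided 0.05, and a 122 that gives exactly 80% or was rounded up from just above 121.

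A reader might go further and call the trial underpowered on this ground. The figures do not support that: the loss is at most about 0.6 points, and it arises only at the edge of a worst case.

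**What to change.** Restate the loss allowance in the Sample size section {14} in one of two ways, without enrolling more patients:

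- 300 patients (150 per group) keep 122 evaluable per group for a loss to follow-up of at most 18.7%; or
- with 20% loss, 300 patients leave 120 evaluable per group and slightly under 80% power (about 79.4% to 79.7%) under the plan's assumptions.

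If the second wording is chosen, the standard deviation behind the 122 would allow a single power figure in place of the range.

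The cost is one sentence. The stated property becomes slightly less favourable. The target, the analysis and the conduct of the trial do not change.
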